**Figure 2 F2:**
[figure not shown]
Decision tree for assigning the clinical outcome state. CTA, CT angiography; ICH, intracerebral haemorrhage; LVO, large-vessel occlusion; MRA, MR angiography; TIA, transient ischaemic attack.

### Study data collection

For patients who give consent for enrolment in the study, data about the blood sampling processes, LVOne test lines status, safety data and routine healthcare information (eg, clinical symptoms, observations, a medical history, medication, laboratory blood test results, primary diagnosis and reperfusion treatments) will be collected. Copies of routine brain images will also be obtained for the neuroradiologist review.

Clinical data will be added to a secure online database managed by the study co-ordinating centre team. Copies of images will be provided on a CD or electronically according to local participating hospital preference. All data will be labelled with a unique study ID number only.

Where tested patients do not give consent to provide data for inclusion in the study, a record of which blood tests were undertaken with date/time and safety data only will be obtained.

### Blinding

The neuroradiologist(s) who reads brain images and the independent stroke clinician(s) who assigns the clinical outcome (reference standard), are blinded to the LVOne test results. Due to the nature of the LVOne test, hospital clinicians are not blinded to these results.

### Staff training and awareness

Study specific training is provided for staff at all participating hospitals by the investigator team.

### Study withdrawal

No specific withdrawal criteria have been preset. Participants may withdraw from the study at any time for any reason. Data collected prior to withdrawal will be used in the study analysis unless the patient or their representative requests that this should not be the case.

### Safety evaluation

This observational study involves fingerprick blood sampling which is a routine clinical procedure and the risks should be no greater than standard care. Any complications of the blood sampling processes are recorded on a paper study record which is completed when patients are having study blood tests undertaken. In addition, this data collection form requests information about any issues which arise during the use of the bespoke lateral flow equipment.

Should a medical event occur which is serious (results in death; is life-threatening; requires inpatient hospitalisation or prolongation of existing hospitalisation; results in persistent or significant disability or incapacity; consists of a congenital anomaly or birth defect and otherwise considered significant by the investigator) and is perceived to be related to the study test, a separate study serious adverse event form will be completed. All such events will be considered ‘unexpected’ and reported to relevant governance bodies.

### Sample size

As the intended purpose of the LVOne test is to ‘rule-in’ patients with LVO stroke, the study sample size calculation is based on demonstrating test specificity.

The sample size calculation is based on a ‘primary analysis population’ which consists of patients scoring 2 or 3 on the FAST clinical symptom scale who are also known to be within 6 hours of symptom onset. This is the population where previous data supports high test accuracy and is, therefore, the most likely future use case for the test, ie, the LVOne test would be deployed if an initial routine FAST test conducted by ambulance practitioners indicates a score of 2 or 3, and the patient is within 6 hours of symptom onset. Considering this primary analysis population, using an estimated prevalence of LVO of 32%, a minimum specificity of 80%, alpha=0.05 and beta=0.1, 123 participants are required to detect a specificity of 92% for LVO versus all other clinical outcomes in the study population.

Due to the nature of this clinical study being conducted in NHS hospitals, some enrolled participant’s data may not be complete for inclusion in the primary analysis, for example, it is not possible to assign a patient as LVO present or absent due to the nature of brain imaging undertaken (see also Reference standards section above). This lack of data is hard to estimate as individual hospital policies vary, however, based on assessment of likely available data from each proposed participating site, the primary analysis population sample size has been initially inflated to 276. During the study, there will be regular monitoring of the number of cases which can contribute to the primary analysis and fewer or additional participants will be sought accordingly.

The population being enrolled in the study is broader than the primary analysis population (as described in the Study population section above) and will include people suspected to be stroke by ambulance practitioners with a score of 1, 2 or 3 on the FAST clinical symptom scale and who are also either known to be within 6 hours of symptoms commencing or last known to be well between 6 and 24 hours ago. This broader study population has been chosen to allow for a number of other important analyses (see also Statistical analysis section below) including:

Confirmation that the LVOne test results are most appropriately used in combination with a FAST score of 2 or 3, rather than FAST 1–3, ie, it is the combination of FAST 2/3, positive d-dimer and negative GFAP which indicates high diagnostic accuracy for LVO detection.Examination of whether or not the combination of FAST 2/3, d-dimer and GFAP is only highly accurate in patients presenting with symptoms known to have begun within 6 hours (data collected about the combination to date) or if it may also be sufficiently accurate to indicate LVO in people where symptom onset is unknown but they were last known to be well between 6 and 24 hours; this reflects increasing evidence of benefit from thrombectomy for people with unknown symptom onset plus favourable findings on advanced brain imaging techniques.

Patients fulfilling the study eligibility criteria but who are outside of the primary analysis population will be tested/consented to the study in parallel with those people who are within the primary analysis population, according to a presentation at participating hospitals and availability of study-trained staff. The number of ‘non-primary population’ participants who will be included in the study is dependent on the number likely to be tested/consented during the time taken to accrue the primary analysis population sample size. This is estimated to be 276 participants.

The overall study population sample size is estimated to be 552 participants.

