### Statistical analysis

All statistical analyses will follow relevant reporting guidelines such as STARD (Standards for the Reporting of Diagnostic Accuracy Studies) 2015^18^ and TRIPOD (Transparent Reporting of a multivariable prediction model for Individual Prognosis or Diagnosis) 2015.^19^

All analyses populations and statistical plans will be fully described in a detailed statistical analysis plan, prepared and finalised prior to the end of data collection.

In addition to the primary analysis population described above (ie, FAST score 2 or 3 and known to be within 6 hours of symptom onset), other analysis populations will examine different combinations of FAST score and time after symptom onset.

According to analyses being conducted, some cases may be excluded with appropriate justification including:

Patients who were enrolled but did not meet a study eligibility criterion and as such were enrolled in error, for example, it only becomes apparent after initial hospital assessment and testing that symptom onset was not within the required boundaries.Patients where a reference standard of ‘ischaemic stroke with unknown LVO status’ is assigned.

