#### Primary analysis

Using the primary analysis population, the accuracy of the LVOne test will be reported as sensitivity, specificity, positive and negative predictive values with 95% CIs. A positive LVOne test is defined as a visible d-dimer line with an intensity score ≥4 out of 10 points (established using the reference scorecard), and an absent GFAP line.

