#### Secondary analyses

Using other analysis populations, the accuracy of the LVOne test will be reported as sensitivity, specificity, positive and negative predictive values with 95% CIs. The analyses of these populations will be conducted and reported in the same way as the primary analysis.

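### The secondary analyses report LVOne accuracy within each FAST group, but the stated aim is to confirm a combined FAST 2/3-plus-LVOne rule, whose specificity and sensitivity in FAST 1–3 are not reported

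*Protocol article*

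**What the plan says.** All references are to the protocol article.

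- **Sample size**, purposes of the broader population: "Confirmation that the LVOne test results are most appropriately used in combination with a FAST score of 2 or 3, rather than FAST 1–3". The same sentence spells this out: "it is the combination of FAST 2/3, positive d-dimer and negative GFAP which indicates high diagnostic accuracy for LVO detection". FAST 2/3 is here one of three components of the rule.
- **Primary analysis** (and the index-test section): "A positive LVOne test is defined as a visible d-dimer line with an intensity score ≥4 out of 10 points", together with an absent GFAP line. FAST is not part of this definition.
- **Statistical analysis**: "other analysis populations will examine different combinations of FAST score and time after symptom onset". FAST therefore enters by choosing who is analysed.
- **Secondary analyses**, on what is to be reported: "Using other analysis populations, the accuracy of the LVOne test will be reported as sensitivity, specificity, positive and negative predictive values with 95% CIs". On the method, the section then adds: "The analyses of these populations will be conducted and reported in the same way as the primary analysis".

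No stated analysis counts FAST 1 patients as negatives of a combined rule, or sets the two rules side by side in the same patients.

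**The concern.** The aim and the stated analysis address different questions. The aim asks whether, among patients with any FAST symptom, requiring FAST 2/3 as well as a positive LVOne is a better rule than LVOne alone. The analysis asks whether LVOne itself is more or less accurate in one FAST group than in another.

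Requiring FAST 2/3 changes specificity because non-LVO patients with FAST 1 become negatives whatever their LVOne result. It changes sensitivity because LVO patients with FAST 1 are no longer detected. Neither effect appears in a table restricted to FAST 2/3, because the FAST 1 patients have left the denominator. A reader who compares the two specificities could see no difference, or the reverse ranking, when the combined rule avoids a material number of false positives. The same reader would not see the LVO cases given up in exchange. Specificity is the measure on which the study is sized, so it is the figure that readers will compare.

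**Working it through.** **The plan's own figure.** "using an estimated prevalence of LVO of 32%, a minimum specificity of 80%, alpha=0.05 and beta=0.1, 123 participants are required" to detect 92%. With the arcsine form of the one-sample test, two-sided alpha 0.05 (sidedness is not stated) and 90% power: n(non-LVO) = ((1.960 + 1.282) / (2·asin√0.92 − 2·asin√0.80))² = 83.95. Dividing by 1 − 0.32 = 0.68 gives 123.5, which agrees with 123. That calculation concerns LVOne within FAST 2/3 and is not in dispute here.

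**Formulas.** Let f0 and f1 be the FAST 1 shares of non-LVO and LVO patients. In FAST 1–3:

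- combined specificity = 1 − FP(FAST 2/3) / non-LVO(FAST 1–3) = 1 − (1 − Sp in FAST 2/3)(1 − f0)
- combined sensitivity = TP(FAST 2/3) / LVO(FAST 1–3) = (Se in FAST 2/3)(1 − f1)
- combined PPV = TP(FAST 2/3) / [TP(FAST 2/3) + FP(FAST 2/3)], which is the PPV of LVOne within FAST 2/3

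**Equal specificity in every stratum.** The documents give neither f0 nor f1. Assume LVOne is 85% specific throughout:

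| Assumed f0 | Planned: FAST 2/3 | Planned: FAST 1–3 | Combined rule in FAST 1–3 |
|---|---|---|---|
| 20% | 85% | 85% | 1 − 0.15 × 0.80 = 88.0% |
| 30% | 85% | 85% | 1 − 0.15 × 0.70 = 89.5% |
| 40% | 85% | 85% | 1 − 0.15 × 0.60 = 91.0% |
| 50% | 85% | 85% | 1 − 0.15 × 0.50 = 92.5% |

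Over the same f0 range, an LVOne specificity of 80% gives 84% to 90%, and 92% gives 93.6% to 96.0%.

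**Reversed ranking.** Assume 263 non-LVO patients with FAST 2/3 (specificity 83%) and 149 with FAST 1 (specificity 90%). The planned tables show 83% in FAST 2/3 and (0.83 × 263 + 0.90 × 149) / 412 = 85.5% in FAST 1–3. The combined rule has 1 − 0.17 × 263 / 412 = 89.1%.

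**Both sides of the trade-off.** Assume all 552 are evaluable, 30% have FAST 1, LVO prevalence is 32% in FAST 2/3 and 10% in FAST 1, and LVOne is 85% specific and 65% sensitive throughout. Non-LVO patients: 262.8 + 149.0 = 411.8. LVO patients: 123.6 + 16.6 = 140.2.

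| | LVOne, FAST 2/3 (planned) | LVOne, FAST 1–3 (planned) | Combined rule, FAST 1–3 |
|---|---|---|---|
| Specificity | 85.0% | 85.0% | 1 − 39.4/411.8 = 90.4% |
| Sensitivity | 65.0% | 65.0% | 80.4/140.2 = 57.3% |
| PPV | 67.1% | 59.6% | 67.1% |

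The planned specificities and sensitivities show no contrast. The planned PPVs do.

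**When FAST carries no information.** Change only the FAST 1 prevalence to 32%, so that f0 = f1 = 30%. PPV is then 67.1% in both populations. The combined rule still moves specificity from 85% to 89.5%, while sensitivity falls from 65% to 0.65 × 0.70 = 45.5%. A gain in specificity alone therefore does not show that FAST helps.

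**The case against.** The strongest reply has four parts.

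1. *Detail belongs in the statistical analysis plan.* The article says "All analyses populations and statistical plans will be fully described in a detailed statistical analysis plan", and that plan, which is not shown, may include the combined rule. The exploratory section also leaves room to relate LVOne to clinical variables. This stands as a caution. It does not remove the point, because the article itself states how these populations will be analysed, and that method does not match the aim it states under Sample size. This is a mismatch between two stated passages, not a missing detail.

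2. *Accuracy within FAST 2/3 is a legitimate quantity.* The Sample size section describes FAST 2/3 as a gate: LVOne would be used once FAST scores 2 or 3. This stands, and the planned analyses should be kept. They do not show what the gate costs and saves, which requires counting the patients it turns away.

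3. *The information is not lost.* The planned PPV in FAST 2/3 is already the combined rule's PPV, and its specificity and sensitivity can be rebuilt from the 2×2 counts of the two populations. This stands. A reader might infer that the study cannot confirm its aim, and the documents do not support that.

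4. *A more specific AND rule is a foregone conclusion.* Adding a condition can never lower specificity or raise sensitivity. This stands too, so the inference that a higher combined specificity proves the value of FAST must also be avoided.

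A reader might further infer that the onset question is to be answered from overlapping populations. The article does not say so; the two onset groups it names are already disjoint. Nor was the second group of about 276 sized for this comparison: it is the number expected to accrue in parallel, and the listed purposes are not said to be the only ones.

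**Conclusion.** The point holds in a limited form. The stated aim concerns a three-part rule, while the sensitivities and specificities in the stated secondary analyses describe LVOne alone within each population. They can show equality, or the reverse ranking, when the combined rule differs from LVOne alone by several percentage points: 3.0 to 7.5 points of specificity at 85% with an assumed FAST 1 share of 20% to 50% of non-LVO patients. Sensitivity falls by the share of detected LVO patients who have FAST 1. These sizes rest on assumed FAST 1 shares and assumed stratum accuracies. The mismatch itself does not depend on them. The primary analysis and its sample size are unaffected. This is an improvement available at almost no cost, not a flaw that prevents the study from answering its question.

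**What to change.** Keep the planned analyses and add the following to the secondary analyses.

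- In participants with FAST 1–3 and known onset within 6 hours, report the accuracy of LVOne positive and FAST 2/3 (FAST 1 counted as negative) beside LVOne alone in the same patients.
- Report the specificity gain and the sensitivity loss together, as paired differences with 95% CIs, plus the PPV of each rule. The two rules can disagree only in LVOne-positive FAST 1 patients, so each difference is a single proportion: false positives with FAST 1 over all non-LVO, and true positives with FAST 1 over all LVO. In the worked case these are 22.4/411.8 = 5.4 points gained and 10.8/140.2 = 7.7 points lost.
- Do not rest the conclusion on a significance test of specificity, since its direction is fixed in advance.
- For the onset question, report the difference in accuracy among FAST 2/3 participants between the two disjoint groups (known onset within 6 hours; last known well 6–24 hours ago) with a 95% CI.

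The cost is one paragraph in the analysis plan, or a check that the plan already contains it. No further data or participants are needed.

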### Statistical analysis

All statistical analyses will follow relevant reporting guidelines such as STARD (Standards for the Reporting of Diagnostic Accuracy Studies) 2015^18^ and TRIPOD (Transparent Reporting of a multivariable prediction model for Individual Prognosis or Diagnosis) 2015.^19^

All analyses populations and statistical plans will be fully described in a detailed statistical analysis plan, prepared and finalised prior to the end of data collection.

In addition to the primary analysis population described above (ie, FAST score 2 or 3 and known to be within 6 hours of symptom onset), other analysis populations will examine different combinations of FAST score and time after symptom onset.

According to analyses being conducted, some cases may be excluded with appropriate justification including:

Patients who were enrolled but did not meet a study eligibility criterion and as such were enrolled in error, for example, it only becomes apparent after initial hospital assessment and testing that symptom onset was not within the required boundaries.Patients where a reference standard of ‘ischaemic stroke with unknown LVO status’ is assigned.

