#### Ischaemic stroke with unknown LVO status

There are likely to be participants with a clinical diagnosis of ischaemic stroke who have not undergone CTA/MRA for some reason. This may be due to the clinical situation (eg, agitation) or local hospital policies about access to this procedure. In these cases, the LVO status is unknown and a separate clinical outcome ‘ischaemic stroke with unknown LVO status’ will be assigned.

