#### Exploratory analyses

Acquired data will drive exploration of relationships which may include those between the diagnoses that constitute the suspected stroke population, LVOne test result, key clinical variables or additional stroke symptom scales (eg, FAST-ED). An alternative reference standard for LVO may be considered, for example, rather than only CT/MR Angiography confirmation, senior clinician assigned ischaemic stroke plus the presence of a dense middle cerebral artery sign on plain CT may be used to indicate LVO for patients who did not have angiography.

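### Leaving ischaemic strokes without angiography out of the primary analysis, while TIAs and mimics without it stay in as non-LVO, may make the accuracy estimates describe a selected subset

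*Protocol article*

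**What the plan says.** All places are in the Protocol article.

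- **Who needs angiography to be classified.** The sections on ischaemic stroke with and without LVO both require CTA or MRA. Where it is lacking, the patient goes into a separate category: "There are likely to be participants with a clinical diagnosis of ischaemic stroke who have not undergone CTA/MRA for some reason". The haemorrhage section needs only CT or MRI. The TIA and mimic sections need a clinician's diagnosis and brain imaging that does not contradict it.
- **Who may leave the analysis.** Under *Statistical analysis*, the permitted exclusions include "Patients where a reference standard of ‘ischaemic stroke with unknown LVO status’ is assigned". Under *Sample size*, the example given of data too incomplete for the primary analysis is that "it is not possible to assign a patient as LVO present or absent due to the nature of brain imaging undertaken".
- **What the study is sized on.** "123 participants are required to detect a specificity of 92% for LVO versus all other clinical outcomes in the study population", with "a minimum specificity of 80%, alpha=0.05 and beta=0.1". To allow for incomplete data, "the primary analysis population sample size has been initially inflated to 276". The number is to be monitored and adjusted in either direction.
- **How angiography comes about.** The section on ischaemic stroke with LVO says it is not routine for every suspected stroke. The *Blinding* section says hospital clinicians are not blinded to LVOne.
- **The only alternative offered.** Under *Exploratory analyses*, a clinician-assigned ischaemic stroke with a dense middle cerebral artery sign "may be used to indicate LVO for patients who did not have angiography".

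**The concern.** Among patients without angiography, the final diagnosis decides who is analysed. An ischaemic stroke may be left out; a TIA or mimic is kept and counted as non-LVO. Haemorrhage is adequately verified by CT, but because it is always kept, its share of the non-LVO group grows when ischaemic strokes leave.

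This matters if false-positive rates differ between these groups. The test calls LVO only when the GFAP line is absent, so haemorrhage and non-LVO ischaemic stroke need not share the same rate.

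There is a second route. The clinicians who order angiography and supply the local diagnosis can see the LVOne result. If it influences either decision, being analysed depends on the index test itself. Blinding the neuroradiologist and the independent stroke clinician cannot recover an angiogram that was never done.

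Specificity, the quantity the study is sized on, is exposed. So are sensitivity, because an LVO without angiography cannot be counted, and PPV and NPV, because they take their prevalence from the analysed subset. The dense-artery alternative can only add LVO-positive cases and leaves the other unknowns out.

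**Working it through.** **1. The plan's own figure.** Inputs from *Sample size*: specificity 92% against 80%, alpha 0.05, power 90%, LVO prevalence 32%. The two-sided arcsine formula gives

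n = [(1.960 + 1.282) / (2 × (asin√0.92 − asin√0.80))]² ≈ 84.0 non-LVO, and 84.0 / 0.68 = 123.5.

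This reproduces 123, so the analysed set would hold about 39 LVO and 84 non-LVO.

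**2. Margin on the primary result.** At 92%, 84 × 0.92 = 77.3 negative readings are expected. An exact binomial test against 80% needs 75 negatives at one-sided 0.025 (p = 0.018) or 74 at one-sided 0.05 (p = 0.037). The article does not say which applies. The margin is 2 to 3 readings, or 2.4 to 3.6 percentage points.

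**3. Size of the allowance.** 1 − 123/276 = 55.4%, or 153 participants, for all causes together.

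**4. Illustration of the selection.** The case mix, false-positive rates and angiography rates here are assumptions; none is in the article. Non-LVO mix: 22% haemorrhage, 30% mimic/TIA, 48% ischaemic. Specificity = 1 − Σ(weight × false-positive rate) / Σ(weight), with the ischaemic weight multiplied by the share who have angiography.

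- Rates 2/6/12%, everyone classified: 1 − (0.0044 + 0.0180 + 0.0576) = 92.0%.
- Same rates, 30% have angiography: 1 − (0.0044 + 0.0180 + 0.0173) / 0.664 = 94.0%.
- Same rates, 10% have angiography: 1 − 0.0282 / 0.568 = 95.0%.
- Rates 2/10/20%: 1 − 0.1304 = 87.0% with everyone classified; at 30%, 1 − 0.0632 / 0.664 = 90.5%.

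On 84 readings, 92.0 to 94.0% is a shift of about 1.7 and 92.0 to 95.0% about 2.6. In the 87.0 to 90.5% case, the expected negatives rise from 73 (below both thresholds) to 76 (above both).

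**5. Angiography following the LVOne result.** Assume, at rates 2/6/12%, that 90% of LVOne-positive and 30% of LVOne-negative ischaemic strokes have angiography.

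- Ischaemic false positives: 0.0576 × 0.9 = 0.0518. Ischaemic true negatives: 0.4224 × 0.3 = 0.1267.
- Specificity = 1 − (0.0224 + 0.0518) / (0.52 + 0.0518 + 0.1267) = 89.4%, against a true 92.0%.
- Sensitivity = 0.62 × 0.9 / (0.62 × 0.9 + 0.38 × 0.3) = 83%, against 62%, the biobank figure in the Introduction.

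The specificity bias is now downward, so its direction is open.

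**6. How many losses step 4 needs.** 276 × 0.68 = 188 non-LVO; × 0.48 = 90 ischaemic; × 0.70 without angiography = 63 patients, or 23% of 276. The effect does not require all 153 to be unknown-LVO strokes.

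**The case against.** **The exclusion is optional, and an analysis plan is promised.** The article says these cases may be excluded, with justification and depending on the analysis, and leaves populations to a separate plan. That is fair: the exclusion is foreseen, not mandated, and the absence of sensitivity analyses from a condensed article is not itself a fault. What stands is the classification rule and the expectation that unknown-LVO strokes will not contribute to the primary analysis. Both are stated, with no other primary handling given.

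**A reader might infer a planned 55% loss to unknown LVO status.** The document does not support this. Unknown status is given as an example, the loss is called hard to estimate, and 276 is an initial figure. The Introduction's rates (40% mimics as the upper figure, 85% of strokes ischaemic) give 0.60 × 0.85 × 276 ≈ 141 ischaemic strokes. Less 39 verified LVO, that leaves about 101 (37%). This is a rough guide, since the FAST 2/3 population may differ.

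**A reader might infer that true prevalence is near 20% and PPV near 66% instead of 78%.** This treats all 153 as unknown ischaemic strokes with 10% LVO, which does not fit the 48% ischaemic share in the specificity illustration. The article also assigns its 32% to the primary analysis population, not to the scanned subset.

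**A reader might see a contradiction in sizing for LVO against all other outcomes.** There is none: the next paragraph of *Sample size* says unassignable patients may be incomplete for the primary analysis.

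**The inputs are invented.** True of the case mix, the false-positive rates and the 90%/30% pattern. Nothing says LVOne guides angiography, only that clinicians are not blinded.

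**Conclusion.** The concern holds as a risk of selection bias in the complete-case estimates. It follows from the stated reference standard, the permitted exclusion, selective angiography and unblinded clinicians. Enrolling more participants does not remove it.

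Direction and size cannot be determined from the document. Under the assumed inputs, specificity is off by about 2 to 3.5 points upward or 2.6 downward, similar to the 2.4 to 3.6 point margin of the primary test. Result-dependent angiography could also inflate sensitivity.

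It would be too strong to say the study will wrongly declare specificity above 80%: true specificity in every scenario shown is 87% or 92%. The supported conclusion is that a complete-case result alone would not show whether the specificity finding is robust.

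**What to change.** Keep the complete-case estimate. For the FAST 2/3, within-6-hour population, report how many patients have unknown LVO status and their LVOne results. Pre-specify beside it:

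- **(a) Bounds**, with all unknowns set to non-LVO and then all to LVO. The all-LVO setting leaves specificity at its complete-case value and moves sensitivity, so both measures should be shown under both settings.
- **(b) A verification-corrected estimate**, by Begg-Greenes or inverse-probability weighting, or by multiple imputation of LVO status from LVOne result, FAST-ED, dense-artery sign, site and reperfusion treatment. Give PPV and NPV at the corrected prevalence as well.

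State in the conclusion whether the specificity result is robust to (a) and (b). The conclusion need not be conditional on the corrected estimate, since (b) relies on data being missing at random.

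Cost: wording in the analysis plan before it is finalised and a few extra analyses of data already collected. The downsides are the missing-at-random assumption in (b) and wider intervals.
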